## Abstract

**Background:**

Alcohol misuse is common in the United Kingdom Armed Forces (UKAF), with prevalence significantly higher than in the general population. To date, digital health initiatives to support alcohol misuse have focused on male individuals, who represent approximately 89% of the UKAF. However, female veterans drink disproportionally more than female members of the public.

**Objective:**

This 2-arm participant-blinded (single-blinded) confirmatory randomized controlled trial (RCT) aims to assess the efficacy of a brief alcohol intervention (DrinksRation) in reducing weekly self-reported alcohol consumption between baseline and a 3-month follow-up (day 84) among women who have served in the UKAF.

**Methods:**

In this 2-arm single-blinded RCT, a smartphone app that includes interactive user-focused features tailored toward the needs of female veterans and designed to enhance participants’ motivations to reduce the amount of alcohol they consume is compared with the UK Chief Medical Officer guidance on alcohol consumption. The trial will be conducted among women who have served at least 1 day of paid service in the UKAF. Recruitment, consent, and data collection will be carried out automatically through the DrinksRation app or the BeAlcoholSmart platform. The primary outcome is change in self-reported weekly alcohol consumption between baseline (day 0) and the 3-month follow-up (day 84) measured using the Timeline Follow Back for alcohol consumption. The secondary outcome is the change in the Alcohol Use Disorders Identification Test score measured at baseline and 3-month follow-up between the control and intervention groups. The process evaluation measures include (1) app use and (2) usability ratings as measured by the mHealth App Usability Questionnaire.

**Results:**

RCT recruitment will begin in January 2024 and last for 5 months. We aim to complete all data collection, including interviews, by May 2024.

**Conclusions:**

This study will assess whether a smartphone app tailored to the needs of women who have served in the UKAF is efficacious in reducing self-reported alcohol consumption. If successful, the digital therapeutics platform could be used not only to support women who have served in the UKAF but also for other conditions and disorders.

**Trial Registration:**

ClinicalTrials.gov NCT05970484; https://www.clinicaltrials.gov/study/NCT05970484

**International Registered Report Identifier (IRRID):**

PRR1-10.2196/51531

## Introduction

### Background

There are 2.5 million military veterans in the United Kingdom (defined by the British government as those who have served in the military for at least 1 paid day), of whom 11% are estimated to identify as female [1]. Female veterans have served in the United Kingdom Armed Forces (UKAF) for >100 years. Although their valuable contribution has been recognized by successive governments and improved military culture. However, with evolving service requirements, they have had a significant impact on the health and well-being of many female veterans [2,3]. Nevertheless, there is a dearth of evidence on the impact of alcohol use on female veterans’ health.

The limited existing evidence suggests that female veterans’ alcohol use is increasing and that they are significantly more likely to report symptoms of hazardous drinking than female civilians [4]. Increased rates of hazardous drinking were also observed by Palmer et al [5], who found that half of the female veterans (389/779, 49.9%) were misusing alcohol at a hazardous or higher level, which is considered harmful to their health [5]. To place this into context, the UK Chief Medical Officer recommends that people do not regularly drink >14 units per week to keep health risks from drinking alcohol to a low level.

Alcohol misuse often co-occurs with common mental health disorders, including posttraumatic stress disorder (PTSD), anxiety, or depression, and alcohol is frequently used as a coping mechanism [2]. Common mental health disorders are more common in female than male veterans [4]. Research has also shown that female veterans face barriers to accessing mental health support, often owing to misusing alcohol [6,7]. Ultimately, although female veterans drink less than male veterans, their rates of hazardous drinking are higher than those of the general population, putting them at increased risk of poorer health.

The impact of alcohol misuse among female veterans on the wider society (eg, health care use, productivity, and welfare) is unknown. In England, heavy drinking (deemed as drinking >14 units of alcohol/wk) is estimated to cost the National Health Service (NHS) £3.5 billion per year (US $3.9 billion; 3.6% of its annual budget) [8] and is more common in people with mental health difficulties [9]. As female veterans drink more than their civilian counterparts, the relative costs are likely to be even higher. Innovative solutions are urgently required.

In recent years, there has been a growing treatment gap in the United Kingdom, with patients waiting longer for treatment and support for alcohol misuse. To overcome this gap, we developed the DrinksRation platform [10], an automated brief digital intervention designed to support help-seeking veterans in managing and reducing the amount of alcohol they drink [11-14]. DrinksRation is unique in that the app content is tailored using behavior change techniques (BCTs) to promote positive changes in behavior. DrinksRation is the only app targeting alcohol misuse in the UKAF community. It is designed to (1) overcome geographic limitations, (2) use wearable technology (eg, Fitbit and Apple Watch) to inform decision-making and personalization, (3) avoid the stigma associated with receiving help in person, and (4) provide convenience because users can use the app as they prefer (discreetly or openly). The app is freely available on the Apple App Store and Google Play Store. The app has received support and endorsement from Combat Stress and is currently being trialed among serving personnel [15]. DrinksRation is supported by a robust evidence base, including a randomized controlled trial (RCT) that demonstrated that the app is efficacious in reducing alcohol consumption [12].

The DrinksRation app was developed to support veterans who have sought help for a mental health problem and was not designed with potential gender differences in mind. A recent viewpoint highlighted a critical need for feminist intersectionality in digital health to incorporate the unique needs of female individuals [16]. Digital health technologies can bolster gender equality through providing increased access to health care, empowering decision-making about one’s health data, overcoming the specific barriers facing female veterans, and reducing the burden on health care systems [17-19].

### Objectives

This project aims to tailor the DrinksRation app to reflect the specific needs of female veterans and evaluate these changes using a confirmatory RCT. It is hypothesized that a refined version of DrinksRation will be efficacious at reducing self-reported weekly alcohol consumption between baseline and the 3-month follow-up (day 84) among female veterans who drink at a hazardous or harmful level.

## Methods

### Ethical Considerations

This study was approved by the ethics committee of King’s College London (LRS/DP-22/23-36879). The study has been registered prospectively on ClinicalTrials.gov (NCT05970484). After completing outcome questionnaires (day 84) at the primary end point (day 84), participants will receive a US $25 (£20 GBP) Love2Shop voucher. There will be no cash alternative offered to participants. We will seek informed consent from all participants via the eligibility and consent survey before the collection of any personal data. For participants in the intervention arm, we will additionally ask for specific on-device permissions to enable the full functionality of the DrinksRation app (eg, to receive push notifications or share health tracking data; refer to the example screenshots presented in Figure 1). Participants can change these optional permissions at any time via the settings page of the app.

Participants will be informed via the participant information sheet that they can withdraw from the study or withdraw from data collection at any time. For participants who withdraw from the study, we will (1) attempt to collect follow-up information if they agree to continued data collection and (2) retain their existing data if they agree to their use. Alternatively, withdrawn participants can delete their study data by contacting the research team. Participants in the control arm will need to withdraw by contacting the research team, whereas those in the intervention arm can withdraw via the app.

If participants in the intervention arm withdraw, they will be asked to delete the intervention app and denied further access. All data, including those from withdrawn participants, except for those who make a request for their data to be deleted, will be included in the final analysis.

**Figure 1 figure1:**
[figure not shown]
Consent flow screenshot examples presented to all study participants.

### Study Design

#### Overview

This is a 2-arm participant-blinded (single-blinded) confirmatory RCT comparing the DrinksRation smartphone app (intervention arm) with a progressive web application (PWA) presenting NHS-focused drinking advice (named *BeAlcoholSmart*; control arm). The DrinksRation app provides individualized normative advice with features designed to enhance participant motivation, interactive feedback, self-efficacy in modifying their alcohol consumption, and personalized gender-specific messaging. We hypothesize that the intervention arm will be efficacious in reducing alcohol consumption compared with the control arm.

Both the control and intervention arms will be delivered digitally. Participants in the control arm will be given access only to a PWA that comprises a calculator for calculating alcohol units consumed over the previous week, generic public health guidance [20], and weekly reminders to use the calculator (refer to the *Control Arm* subsection for details). Participants in the intervention arm will be given access to the full enhanced DrinksRation app, which includes a range of theoretically driven features and behavioral change messaging (discussed further in the *Intervention Arm* subsection). We have designed this study so that the control arm resembles the intervention arm (eg, an app delivered digitally and usable on a smartphone) but lacks the active ingredients present in the DrinksRation intervention arm (eg, a drinks diary, interactive drinking feedback, and goal setting). This approach was selected to ensure consistency between the arms (both groups receive a digital intervention) and to facilitate participant blinding to treatment assignment.

Participants in both arms will be asked to use the digital interventions for 12 weeks (the intervention period; 84 days). Figure 2 presents the study flow and data collection points.

**Figure 2 figure2:**
[figure not shown]
Study flow diagram. Primary outcome is assessed at day 84.

#### Intervention Arm

The DrinksRation (formerly called *InDEx* [13,14,21]) app was developed following the Medical Research Council’s guidelines for developing and evaluating complex interventions and using a co-design methodology. It was developed by the King’s Centre for Military Health Research (King’s College London) and Lancaster University with support from experts in smartphone app development, epidemiology, addiction psychiatry, and military mental health. The app is designed to support veterans drinking at a hazardous or harmful level by providing bespoke advice and support.

The app seeks to enhance participants’ motivation and self-efficacy in modifying their alcohol consumption using BCTs presented via the in-app content (Multimedia Appendix 1) and through messages sent to participants. The iterative development process, theoretical framework, feasibility trial, pilot, and RCT are reported elsewhere [11-14,21]. Briefly, DrinksRation was developed and tested with 5 core modules (Textbox 1; refer to Figure 3 for example screenshots).

The app is compatible with all modern iOS- and Android-supported devices. Participants in the intervention arm will complete all questionnaires via the app, including additional questionnaires on their mood and general mental health, which are used to personalize the app content and push notifications. Participants will receive push notifications every few hours on the day that each questionnaire is due to prompt the completion of unanswered questions.

Core modules of the DrinksRation app.
**Account management**
Participants can modify personal information (eg, first name and mobile phone number) and app parameters (eg, automatic log out, data-sharing permission, and withdrawing from the study).
**Questionnaire and individualized normative feedback**
This feature captures the participant’s responses to a set of questions and aggregates the responses to produce personalized feedback on drinking behaviors.
**Self-monitoring and feedback**
This feature records alcohol consumption by participants and provides a range of visual illustrations (eg, charts, figures, and text) to allow for the monitoring of consumption. Furthermore, the participant can select visual metrics relevant to their interest (eg, calories, cost, and exercise required).
**Goals (setting and review)**
Participants can set goal or goals based on the implementation intentions (if and then) [22] methodology; visual feedback provides feedback on progress toward achieving the goal or goals set.
**Personalized messaging**
Participants are sent tailored messages via push notification, which provide prompts to use the drinks diary, suggest alternative behaviors, and provide feedback on goals.

**Figure 3 figure3:**
[figure not shown]
Example screenshots of the DrinksRation app.

#### Control Arm

The control arm will receive access to the BeAlcoholSmart PWA. A PWA is a website that looks and behaves like a smartphone app. The PWA can take advantage of smartphone features such as push notifications and haptics without requiring the participant to download it via an app store. The BeAlcoholSmart PWA will be accessible to participants in the control arm via a unique link. The app will contain a 7-day alcohol unit calculator and generic public health guidance on safe drinking [20]. Participants will also receive reminders via email prompting them to consult the guidance provided as part of the BeAlcoholSmart PWA. Control participants will be invited to complete all questionnaires via Qualtrics (Qualtrics International Inc), with an email reminder being sent when they are due.

### Participant Co-Design

This study will evaluate an adapted version of the DrinksRation app that caters to the specific needs of female veterans. To ensure that any adaptations and new features are suitable for the target population, we will undertake participatory research—following the guidelines provided in the study by Bell and Pahl [23]—in the form of co-design and cocreation via a patient advisory board (PAB) and a stakeholder advisory board (SAB). The PAB will include those with lived experience of military service, whereas the SAB will include stakeholders and those representing the target population, such as charities treating alcohol misuse. PAB and SAB members will be recruited via our existing networks and communication channels.

We aim to recruit up to 5 members on both the PAB and SAB. Before undertaking any data collection, we will hold 2 roundtable discussions to collect input on the (1) development of app content, (2) refinement of existing app content, (3) development of new app features, and (4) suitability of tailored messaging.

In addition to PAB and SAB discussions, we will also ask members of the PAB to provide iterative feedback on updates to the DrinksRation app, study protocol, and study findings. Furthermore, we will hold a PAB and SAB meeting every quarter to provide updates on the study progress and to promote research awareness. PAB members will receive a US $13 (£10 GBP) digital Love2Shop voucher for each video session they attend. It is important to note that PAB members will not be allowed to participate in the RCT.

### Eligibility Criteria

The eligibility criteria are provided in Textbox 2.

Inclusion and exclusion criteria.
**Inclusion criteria**
Aged ≥18 yearsIdentify as female (self-reported sex)Live in the United KingdomConsume ≥15 UK units (approximately 150 g) of alcohol/wk as measured using Timeline Follow Back for alcohol consumption [24] at baseline (day 0; the choice of a minimum threshold of 15 UK units of alcohol/wk reflects scientific research and UK national guidelines that indicate that regular drinking of >15 units/wk carries increased health risks [25])Are veterans of the United Kingdom Armed Forces (UKAF), defined as per UK definitions as having completed at least 1 day of paid employment in the UKAF (verified by self-report at eligibility screening)Have downloaded the mobile app onto an iOS or Android smartphone
**Exclusion criterion**
Do not own a smartphone

### Sample Size Calculation

A power calculation was performed based on previously reported data from the DrinksRation RCT [12]. With 148 participants (n=74, 50% per arm), we will have at least 80% power to detect a difference in alcohol consumption of 3 units (approximately 30 g of alcohol/wk) between the intervention and control arms at the 84-day follow-up assessment. This calculation assumes an SD of 5.6 units, an attrition rate of 40% by day 84, a correlation between successive follow-up assessments of 0.7, and an α of 5%.

We have chosen a minimum difference of 3 units based on treatment effects observed in similar studies [26-28] and in reductions observed in the DrinksRation feasibility trial [11] and the confirmatory RCT among help-seeking veterans [12], which found reductions at 28 days of 22 units between the arms. We have chosen a smaller minimum difference of 3 units, recognizing that treatment effects for brief interventions reduce over time and that the target population for this study is not a help-seeking population.

### Recruitment

Participants will be recruited via an existing research cohort [26] and social media [29] following published recruitment strategies [29,30]. The research cohort will comprise participants from the King’s Centre for Military Health Research health and well-being longitudinal cohort study [26], and participants will be sent an email inviting them to take part. We will also seek to recruit participants via paid promotional advertisements on social media (eg, Twitter, Facebook, and Instagram) with a link enabling potential participants to complete the eligibility and consent survey.

Potential participants who respond to the email invitation or social media advertisements will be sent an email containing an explanation of the study, a link to the participant information sheet, and an invitation to complete the eligibility and consent survey (Multimedia Appendix 2). Eligible participants will then be randomized (refer to the Randomization and Blinding subsection) and sent instructions on accessing the BeAlcoholSmart or DrinksRation app using a unique QR code. Once they have accessed the platform, they can register an account and complete the baseline questionnaire (day 0).

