**Remote data collection (continuous)**																																			
	Wearable sensors^j^	✓		✓		✓			✓		✓			✓		✓			✓		✓			✓		✓			✓		✓			✓	
	Smartphone sensors^j^	✓		✓		✓			✓		✓			✓		✓			✓		✓			✓		✓			✓		✓			✓	

^a^I: intervention arm data collected via app.

^b^C: control arm data collected via Qualtrics (Qualtrics International Inc) through BeAlcoholSmart platform.

^c^PHQ-2: Patient Health Questionnaire-2.

^d^GAD-2: Generalized Anxiety Disorder-2.

^e^ITQ-PTSD: International Trauma Questionnaire for Posttraumatic Stress Disorder.

^f^AUDIT: Alcohol Use Disorders Identification Test.

^g^TLFB: Timeline Follow Back.

^h^A total of 10 participants will be invited to participate in a qualitative interview after day 84.

^i^MAUQ: mHealth App Usability Questionnaire.

^j^Additional participant consent is required.

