#### Baseline Measures

After they have downloaded the respective platforms, participants will be asked to complete a baseline questionnaire to assess physical and mental health, readiness to change, self-efficacy, health status, and sociodemographics (eg, age, gender, ethnicity, employment status, and occupation). The questionnaire set is available in Multimedia Appendix 3, and the schedule is presented in Table 1.

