#### Outcome Measures

The primary outcome in this study is self-reported alcohol consumption measured by the 7-day Timeline Follow Back for alcohol consumption. At baseline (day 0) and 28, 56, and 84 days after randomization, participants will be asked to report the number and types of drinks that they consumed in each of the previous 7 days via DrinksRation or BeAlcoholSmart. Using standard unit measurements (Multimedia Appendix 4), we will calculate weekly alcohol consumption for baseline and each follow-up by summing the number of units assigned to each drink. To maximize the completion of the primary outcome at each follow-up, participants will first be asked to complete the primary outcome measure before completing the rest of the questionnaire. The secondary outcome is the change in the Alcohol Use Disorders Identification Test score, measured at baseline (day 0) and day 84 follow-up between the control and intervention groups.

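### The drinking measure that sets eligibility and serves as baseline covariate is collected only after randomisation, on arm-specific platforms, so the entry criterion cannot be applied before allocation

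*Protocol article*

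**What the plan says.** The inclusion criteria (Textbox 2) require at least 15 UK units a week, "as measured using Timeline Follow Back for alcohol consumption [24] at baseline (day 0"). They also require that participants "Have downloaded the mobile app onto an iOS or Android smartphone".

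The Recruitment section gives the order of events. After the eligibility and consent survey, "Eligible participants will then be randomized (refer to the Randomization and Blinding subsection) and sent instructions on accessing the BeAlcoholSmart or DrinksRation app". Then: "Once they have accessed the platform, they can register an account and complete the baseline questionnaire (day 0"). The Baseline Measures section agrees: "After they have downloaded the respective platforms, participants will be asked to complete a baseline questionnaire".

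The TLFB is collected on the arm's own platform. Under Outcome Measures, at day 0 and each follow-up, "participants will be asked to report the number and types of drinks that they consumed in each of the previous 7 days via DrinksRation or" the control platform. A footnote to Table 1 describes the intervention arm's entries as "intervention arm data collected via app"; the Control Arm section and the next footnote put the control arm's questionnaires in Qualtrics.

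The Statistical Analysis section enters the day-0 value of the outcome as a covariate in the linear mixed model for the primary outcome.

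**The concern.** Two statements cannot both be followed. The Recruitment section says "Eligible participants will then be randomized", but the drinking value that defines eligibility does not exist at that moment. It arises later, on a platform that depends on the allocation. The download criterion has the same ordering conflict: access instructions go out only after randomisation, and the Control Arm section describes a web application that needs no app-store download.

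Three things are at stake. First, a randomised participant who reports fewer than 15 units on day 0 breaches the criterion if kept and becomes a post-randomisation exclusion if removed. Second, someone who is randomised but never registers has no baseline. The registration step differs by arm (installing an app or opening a link), and so does prompting (push notifications every few hours or an email reminder). Third, covariate adjustment is protected by randomisation only if allocation cannot affect the covariate. A value collected after allocation, by app in one arm and Qualtrics in the other, does not carry that guarantee.

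**Working it through.** **Sequence, from the sections quoted above**

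1. Eligibility and consent survey, common to both arms.
2. Randomisation by token.
3. Instructions and QR code for the allocated platform.
4. Registration on that platform.
5. Day-0 questionnaire with the TLFB, by app or by Qualtrics.

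The 15-unit criterion is defined at step 5 but is needed at step 2. Two sections (Recruitment and Baseline Measures) give the same order, so this is not one loose sentence. The article states no separate TLFB before randomisation.

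**The plan's own figure**

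Inputs from Sample Size Calculation: difference 3 units, SD 5.6, correlation between successive follow-ups 0.7, attrition 40%, α 5% (taken as two-sided), power 80%.

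- Variance of the mean of three follow-ups: 5.6² × (1 + 2 × 0.7)/3 = 31.36 × 0.8 = 25.09.
- n per arm = 2 × (1.960 + 0.842)² × 25.09 / 3² = 43.8, rounded up to 44.
- With attrition: 44 / 0.6 = 73.3, rounded up to 74 per arm, 148 in total.

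The stated 148 is reproduced. The sample size is not in question, and the fix does not change it.

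**Possible movement of the adjusted effect (assumed inputs)**

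Let the intervention platform shift the reported day-0 value by δ units, let b be the slope of follow-up on baseline, and let the true treatment effect be zero. The adjusted difference is (difference in follow-up means) − b × (difference in baseline means). Neither δ nor b is in the article. The value b = 0.7 is an assumption; the protocol's 0.7 is a correlation between successive follow-ups, not a baseline slope.

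| Case | Formula (absolute size) | δ = 1 | δ = 2 |
|---|---|---|---|
| No shift | 0 | 0 | 0 |
| Shift at baseline only | b × δ | 0.7 | 1.4 |
| Same shift at baseline and follow-up | (1 − b) × δ | 0.3 | 0.6 |

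Against the 3-unit target, the baseline-only case is 0.7/3 = 23% to 1.4/3 = 47%, in the direction opposite to the shift. The persistent case is 0.3/3 = 10% to 0.6/3 = 20%, in the direction of the shift. A simulation under the null with SD 5.6, correlation 0.7 and assumed means of 18, 20 and 25 units gave about 0.7 and 1.4 for the baseline-only case and about zero for no shift, with or without a 15-unit cut after randomisation.

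**Share below 15 units on day 0 (assumed means)**

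This assumes a normal distribution with SD 5.6 and no earlier drinking screen: P(X < 15) = Φ((15 − mean)/5.6).

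- Mean 18: Φ(−0.54) = 30%.
- Mean 20: Φ(−0.89) = 19%.
- Mean 25: Φ(−1.79) = 4%.

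Any drinking screen in the eligibility survey would lower these shares.

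**The case against.** A reader might infer that the trial plans to exclude people after randomisation. The article does not say so. Ethical Considerations keeps all data except those that participants ask to have deleted, and the primary analysis includes everyone with at least one follow-up. The exclusion is one of two ways out of the conflict, not a stated step.

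A reader might also infer that entry demonstrably depends on allocation, or that the primary estimate is biased. The text supports neither. The eligibility questionnaire (Multimedia Appendix 2) is not shown and may include a drinking screen. Allocation is automated and future allocations cannot be seen. The TLFB looks back over 7 days and Table 1 counts days from randomisation, so a day-0 report made on time describes drinking before platform access. The app's normative feedback is built from the answers and so follows them. What remains is a difference in reporting mode, late registration, and unequal completion of day 0. The article gives no size for any of these.

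The strongest point concerns the baseline-only calculation. Each arm keeps its own mode at follow-up, so a mode effect would plausibly persist. The present design then carries (1 − b) × δ, or 0.3 to 0.6 units. With a common pre-randomisation baseline and follow-up still arm-specific, the same persistent shift would appear in full, 1 to 2 units. Moving the baseline alone would therefore make this particular bias larger.

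These points limit the size and certainty of the concern. They do not remove the conflict. Even if Appendix 2 screens drinking, Textbox 2 ties the threshold to day 0, and the covariate is still collected after allocation. Nor can the analysis later supply a pre-randomisation baseline that was never collected.

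**Conclusion.** The concern holds as a conflict of sequence. The 15-unit criterion and the download criterion, as worded, cannot be checked before allocation, and the baseline covariate is a post-allocation measurement taken by different modes in the two arms. That much rests only on the article's text.

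Whether it biases the result is unknown. The illustrative range runs from zero to 1.4 units against a 3-unit target. The upper end needs a 2-unit shift confined to baseline and b = 0.7, neither of which the article supports. The share of participants affected by the threshold conflict could run from about 4% to 30%, depending on mean intake, if nothing screens drinking earlier. The point should be settled before recruitment because it cannot be repaired afterwards.

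**What to change.** - Put the 7-day TLFB in the common eligibility and consent survey, identical for everyone.
- Issue the randomisation token only after the TLFB is submitted and at least 15 units is confirmed.
- Use that value both for eligibility and as the baseline covariate.
- State that all randomised participants are kept, whatever they later report on the platform.
- Reconcile the Inclusion criteria, Recruitment and Baseline Measures sections, and reword the download criterion so that it can be checked before allocation.
- Ask the TLFB in the same format in both arms at all time points. Without this, moving the baseline leaves any app-versus-Qualtrics difference at follow-up in full.

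The eligibility survey and the automated token already exist, so this is largely a re-ordering and a wording amendment, and the sample size stays at 148. The costs are a slightly longer screening survey, which may lose some people before randomisation rather than after it, the work of passing the baseline answers to the app, which uses them to tailor messages, and the work of aligning the TLFB format across the two platforms.
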